### Planned Analyses

As this study is a pilot study designed to generate initial data to guide future research, a power calculation has not been conducted. A sample size of 10 participants is consistent with similar proof-of-concept and pilot studies [44,48].

### Primary Analyses

Means and SDs of acceptability, feasibility, safety, and usability measures and the percentage of participants showing different levels of ratings on the Pilot Study Assessment Instrument will be reported. Thematic analysis of the semistructured interviews will also be conducted. The number of adverse events and serious adverse events will be reported and reviewed.

### Secondary Analyses

#### Clinical Efficacy

Effect sizes, paired *t* tests and Wilcoxon analysis of clinical rating changes before and after the intervention will be computed, which will inform future efficacy trials.

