**Methods:**

Hybrid takes a “symptom capture” approach using individually tailored VR-based exposure exercises. Participants (N=10) will receive the intervention package weekly over 12 face-to-face sessions. Here, participants will be progressively exposed to symptom triggers and develop methods of downregulating neural activity associated with these symptoms (neurofeedback component) while concurrently receiving clinician-delivered cognitive behavioral therapy for psychosis.

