### The Hybrid Study

This study, Hybrid, will investigate the potential of a novel treatment approach to AVH in young people with FEP that, if successful, could be incorporated into an individual’s broader health care program. Our integrative model combines psychological therapy (CBTp), new immersive technologies (VR), and neuroscience (neurofeedback) in an individualized symptom capture (or ERP) treatment approach. The term “Hybrid” is used to reflect the integrated approach of treatment where each element has been selected to strengthen the effectiveness of the treatment regime as a whole.

A pilot study is required to investigate the following aims: (1) to determine whether Hybrid is feasible, acceptable, and safe; (2) to examine participants’ experience of the intervention package and whether it can be modified to increase probability of clinical utility; (3) to explore if there is a signal of clinical benefit in response to Hybrid treatment; and (4) to examine whether Hybrid engages specific neural (modulating high β band activity) and psychological (moving up a symptom-eliciting exposure hierarchy) targets (proof of concept). Hybrid will be an unblinded, single-arm intervention study.

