##### Safety of the Hybrid Model

Safety will be assessed by recording adverse events or serious adverse events.

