#### Further Analyses

Whether greater engagement of neural and psychological targets is associated with greater change in clinical measures will also be explored. This finding would indicate a treatment mechanism that could be systematically tested in future studies.

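### The stated safety outcome leaves out the symptom ratings, so no stated analysis counts participants whose voices worsened under a treatment that deliberately elicits voices

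*Protocol article*

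**What the plan says.** All references are to the protocol article.

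- **Treatment.** In the abstract's Methods, "participants will be progressively exposed to symptom triggers". *Feasibility and Acceptability of the Hybrid Model* adds that eliciting voices at a high rate is needed for the therapy to work as intended.
- **Safety outcome.** *Safety of the Hybrid Model*: "Safety will be assessed by recording adverse events or serious adverse events". *Primary Analyses*: "The number of adverse events and serious adverse events will be reported and reviewed". Perceived safety is also self-rated on the Pilot Study Assessment Instrument, and a survey rating of safety enters the 70% progression rule under *Threshold of the Hybrid Model*.
- **Symptom ratings.** The PSYRATS hallucinations scale, PANSS and BPRS are secondary outcomes. Under *Clinical Efficacy*, Wilcoxon tests, paired t tests and effect sizes are named for them: "analysis of clinical rating changes before and after the intervention will be computed, which will inform future efficacy trials". Their one other stated use is under *Further Analyses*: "Whether greater engagement of neural and psychological targets is associated with greater change in clinical measures will also be explored".
- **Design.** "Hybrid will be an unblinded, single-arm intervention study", with 10 participants and no power calculation.

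**The concern.** When a treatment provokes a symptom, worsening of that symptom is the most foreseeable harm. The trial measures the symptom on a scale covering severity, frequency and distress, but the article assigns those scores to efficacy and mechanism and not to safety. Under *Clinical Efficacy*, improvers offset those who deteriorate. Under *Safety of the Hybrid Model*, worsening is seen only if someone records it as an adverse event, and the article does not say whether a worsened rating counts as one.

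At stake is the safety conclusion behind the move to efficacy trials. A report that follows the article could show few adverse events and a favourable average change without saying how many participants ended with worse voices, although the data to say so are already collected.

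**Working it through.** The article gives no alpha, power, effect size or SD, so there is no figure of its own to reproduce. The only document inputs are n=10, the single arm, the two planned tests and the 70% rule. All change scores and effect sizes below are assumptions chosen to show the mechanism.

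**1. Can the paired t test be favourable while some participants worsen?** Suppose 8 improve by 6 points and 2 worsen by 3.

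- Mean improvement = (8×6 − 2×3)/10 = 4.2.
- Sum of squares = 8×1.8² + 2×7.2² = 25.92 + 103.68 = 129.6, so SD = √(129.6/9) = 3.79.
- t = 4.2/(3.79/√10) = 3.5 on 9 df, p=0.007; standardised effect = 4.2/3.79 = 1.11.

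**2. Does the rank test behave differently?** Two more varied sets, with negative meaning improvement:

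| Change scores | Worse | Mean | SD | Mean/SD | t test p | Wilcoxon p |
|---|---|---|---|---|---|---|
| −12, −11, −10, −9, −9, −8, −7, −6, +5, +6 | 2 of 10 | −6.1 | 6.37 | −0.96 | 0.014 | 0.012 |
| −12, −11, −10, −9, −9, −8, −7, +3, +4, +5 | 3 of 10 | −5.4 | 6.65 | −0.81 | 0.030 | 0.025 |

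Both tests favour the treatment in both sets, so adding Wilcoxon does not close the gap.

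**3. How often might a score fall below baseline?** If change is normal with mean improvement dz (in SDs of change), P(worse) = 1 − Φ(dz), and the chance of at least one in 10 is 1 − (1 − P)^10.

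| dz | P(worse) | Expected worse of 10 | Chance of at least one |
|---|---|---|---|
| 0.5 | 0.309 | 3.1 | 97.5% |
| 0.8 | 0.212 | 2.1 | 90.8% |
| 1.0 | 0.159 | 1.6 | 82.2% |

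These count any worsening, measurement noise included. They are not counts of clinically important deterioration.

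**4. Does the progression rule catch it?** It uses no symptom score. It needs 70% of participants, that is 7 of 10, so 3 could rate safety below 3 and the rule would still be met.

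**5. What could a count of worsened participants show?** Exact (Clopper-Pearson) 95% intervals:

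| Worsened | 95% CI |
|---|---|
| 0/10 | 0 to 30.8% |
| 1/10 | 0.3 to 44.5% |
| 2/10 | 2.5 to 55.6% |
| 3/10 | 6.7 to 65.2% |

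For 0/10 the upper limit is 1 − 0.025^(1/10) = 0.308.

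**6. Who might be missing from the comparison?** The abstract's Results report that 1 of 5 starters had withdrawn, with no reason given. *Data Management and Imputation Strategy* imputes only if missing data are substantial. A before-and-after comparison may therefore omit people who stopped, including any who stopped because of symptoms.

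**The case against.** The strongest reply is that this is a condensed article. Individual listings, deterioration margins and the adverse event definition commonly sit in the full protocol or SAP, which are not shown. If symptom exacerbation is defined there as an adverse event, much of the concern goes. This stands as a limit on what can be claimed. It does not dispose of the point, because the article is not silent: it states what safety consists of and places the ratings under efficacy.

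A reader might infer that participants who worsen would go unseen altogether. The documents do not support that. Adverse events are reviewed as well as counted, perceived safety is reported as percentages at each rating level, dropouts and attendance are assessed, and the exit interviews are analysed thematically. A therapist is present at every session. Marked worsening has several routes to being noticed. That gradual worsening would escape adverse event reporting is an inference, not a statement in the article.

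Nor are the ratings used only as averages: Wilcoxon works on ranks, and the *Further Analyses* association uses each participant's change. Both still yield group summaries, not a count of who worsened.

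It is also fair that the example scores are invented, that the article gives no SD or reliability for PSYRATS from which to set a margin, and that worsening in one arm cannot be attributed to treatment. The last limit applies equally to adverse event counts, which the plan nevertheless reports.

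**Conclusion.** The point holds as a weakness in the stated choice of safety measures, and the remedy is an inexpensive improvement. Safety, a primary aim, is assessed without the ratings that measure the most foreseeable harm directly, and no stated analysis counts participants who worsened. At n=10 both planned tests can be favourable at p<0.05 with 2 or 3 participants worse. That is a demonstration on assumed scores, not a forecast.

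The article does not support saying that 20% to 30% of participants will deteriorate, that worsening would be caused by the treatment, or that it would necessarily be missed. How much rests on the symptom ratings depends on an adverse event definition that the article does not give.

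**What to change.** Add to *Primary Analyses*, beside the adverse event and serious adverse event listing:

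- each participant's PSYRATS hallucinations score (total and distress items) and PANSS and BPRS totals, before and after treatment;
- the number and percentage, with exact 95% CI, who worsened by more than a margin fixed before the data are analysed;
- worsening of any size, shown descriptively only because it includes noise;
- participants who stopped because of symptom worsening, listed with those who worsened.

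State whether a worsened rating is recorded as an adverse event. State also that a single arm of 10 cannot attribute worsening to treatment, and that 0 of 10 still leaves an upper 95% limit of about 31%.

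The cost is a few lines of text and one small table, with no new assessments. The reason for stopping must be on record, and the margin must be agreed in advance. The downside is that the safety result may look less favourable than adverse event counts alone, and small counts will carry some measurement noise.

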#### Target Scores

Means, SDs, and 95% CIs of neural (average β band power) and psychological (exposure hierarchy level) target scores will be reported. The magnitude of the changes in both scores will reflect the degree of target engagement achieved. A mean score will be used for analysis and will be given by the average change over the first half (mean of weeks 3 to 8) and second half (mean of weeks 9 to 14) of the sessions attended.

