#### Virtual Reality

The VR paradigm that will be used to elicit AVH is inspired by Stinson et al [59] who used a real-world setting comprising computer-generated characters of both sexes and several ethnicities and background sounds simulating the environment. Our VR approach is based on the CBTp framework, beginning with developing a shared understanding (functional analysis) between the participant and therapist of the antecedents of hallucinatory episodes (eg, presence of other people and lack of meaningful activity) and habitual responses to them (eg, talking back to voices, avoidance). The participant and therapist will then select a template scenario from preexisting VR environments (eg, supermarket and bedroom) developed in consultation with a small group of current and previous service users. Various aspects of the VR environment will be modified to personalize it for the antecedents the individual has identified and to create a hierarchy of symptom-provoking situations. These will include such aspects as the number of people present, proximity and gaze intensity of people, context (interpersonal interaction, indoors, outdoors, time of day or night), sounds, and the presence or absence of “safety strategies” to manage symptoms (eg, mobile phone). For each participant, there will be 5 scaled variants of the personalized scene graded on a 0-100 scale of subjective distress (ranging between 0 and 20 [low], 21 and 40 [moderate], 41 and 60 [high], 61 and 80 [very high], and 81 and 100 [severe]). There are a number of benefits of the VR approach. (1) It provides a controlled environment that can be stopped at any moment, which is not always feasible in real-life exposure settings. (2) It can be designed in a manner that is highly personalized to the individual, which may maximize therapeutic potential. (3) It is a treatment approach that may be particularly suited to young people, given its engaging and interactive nature. (4) It is becoming increasingly feasible for translation into clinical services, given the dramatic reduction in the cost of VR equipment and the fact that VR devices are becoming increasingly portable.

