### Implementation Phase (Weeks 3-14)

The implementation phase will consist of weekly sessions delivered over a 12-week period (SD 14 days, Figure 2) and consists of the following two components: (1) CBT in vivo (in response to the VR exposure) and (2) neurofeedback simultaneously presented to the participant via the VR device. The VR apps and sessions can only be accessed by the clinician and administered in person. During these weekly sessions, the therapist will be able to view the VR scenario (via an external monitor) and the neurofeedback thermometer, hear the auditory input, and provide guided assistance to the individual.

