### Cognitive Behavioral Therapy in Vivo (in Response to VR Exposure)

The participant will start at the lowest level of their exposure hierarchy and progressively work up the hierarchy over the course of the sessions. The standard approach in ERP interventions will be adopted, which is to achieve a reduction in subjective units of distress to 30/100 before progressing to the next step in the hierarchy. While the participant is exposed to the symptom-eliciting VR scenario, they will engage in CBTp with their therapist (the participant will be wearing “open backed” headphones, allowing them to hear the therapist as well as sounds coming from the VR environment). The CBT will be standard, manualized CBT for voices [64,66,67] dealing with the “hot” cognition reactions elicited by the VR scenario. Key elements include reassurance regarding lack of threat, challenging appraisals of AVH (eg, their perceived power, threat, or dominance; reducing submissive or reactive behaviors), actively responding to AVH, and developing a sense of control over AVH by attempting to delay or reduce their volume or distract from them with a variety of strategies (eg, humming and visualization). Sessions will last 30-45 minutes and will be stopped at any point if requested by the participant.

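### For the exposure hierarchy, the change between weeks 3-8 and weeks 9-14 is a poor engagement score: with only five levels, climbing early lowers it

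*Protocol article*

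**What the plan says.** The protocol article, under Target Scores, treats the neural and the psychological (hierarchy level) scores alike. The score is defined as "average change over the first half (mean of weeks 3 to 8) and second half (mean of weeks 9 to 14) of the sessions attended", and the reading given to it is that "The magnitude of the changes in both scores will reflect the degree of target engagement achieved".

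The hierarchy is bounded. The Virtual Reality part of the treatment model states that "there will be 5 scaled variants of the personalized scene". On movement through it, the section on CBT in vivo says: "The participant will start at the lowest level of their exposure hierarchy and progressively work up the hierarchy over the course of the sessions". The condition for moving up is to "achieve a reduction in subjective units of distress to 30/100 before progressing to the next step in the hierarchy". No limit on levels gained per session is stated. The implementation phase consists of "weekly sessions delivered over a 12-week period", that is, six sessions in each half.

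The Psychological Treatment Target section takes the highest level in each session as the measure, but summarises it differently, as the participant's average over the 12 sessions. Target Scores does not mention that definition.

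The score is then used again under Further Analyses: "Whether greater engagement of neural and psychological targets is associated with greater change in clinical measures will also be explored".

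**The concern.** A change between two halves measures how much of the climbing falls late in the course. It does not measure how far a participant climbed. On a scale that stops at 5, a participant at the top before week 9 cannot rise further, and every early session at a high level is subtracted from the score. A larger change therefore need not mean greater engagement.

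Moving up the hierarchy is half of the proof-of-concept aim, and the article says that an association between engagement and clinical change would point to a treatment mechanism. With 10 participants, one or two people placed in the wrong order could noticeably alter that association. Settling the disagreement between the two sections in favour of the half-versus-half change would keep the problem.

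**Working it through.** The article gives no target-score figure to reproduce. The check applies its rules to possible session-by-session paths.

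**Inputs**
- Levels 1 to 5 (Virtual Reality).
- Start at the lowest level and move upward (CBT in vivo).
- 12 weekly sessions; weeks 3-8 are sessions 1-6 and weeks 9-14 are sessions 7-12 (Implementation Phase; Target Scores).
- Measure: highest level in each session, L1 to L12 (Psychological Treatment Target).
- Assumptions: all 12 sessions attended, no moves down, and, unless stated, level 1 in session 1 and at most one level gained per session.

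**Formulas**
- Change score (Target Scores): C = (L7 + ... + L12)/6 - (L1 + ... + L6)/6.
- Average score (Psychological Treatment Target): A = (L1 + ... + L12)/12.

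With the other sessions fixed, one extra level in any of sessions 1-6 lowers C by 1/6 and raises A by 1/12. For anyone at level 5 throughout sessions 7-12, C = 5 minus the first-half mean, so the faster the climb, the lower C.

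**Results** (sessions 1-6 | sessions 7-12)

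| Path | First-half mean | Second-half mean | C | A |
|---|---|---|---|---|
| Fastest completer: 1,2,3,4,5,5 \| 5,5,5,5,5,5 | 20/6 = 3.33 | 30/6 = 5.00 | +1.67 | 50/12 = 4.17 |
| Completer, two sessions per level: 1,1,2,2,3,3 \| 4,4,5,5,5,5 | 12/6 = 2.00 | 28/6 = 4.67 | +2.67 | 40/12 = 3.33 |
| Three sessions per level, never reaches 5: 1,1,1,2,2,2 \| 3,3,3,4,4,4 | 9/6 = 1.50 | 21/6 = 3.50 | +2.00 | 30/12 = 2.50 |
| Late climb to level 3: 1,1,1,1,1,1 \| 2,3,3,3,3,3 | 6/6 = 1.00 | 17/6 = 2.83 | +1.83 | 23/12 = 1.92 |
| Late move to level 2: 1,1,1,1,1,1 \| 2,2,2,2,2,2 | 6/6 = 1.00 | 12/6 = 2.00 | +1.00 | 18/12 = 1.50 |

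By C, the fastest completer comes below the slower completer and below two participants who never finish. By A, the order is fast completer, slower completer, steady non-finisher, level 3, level 2.

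**Limits of the reversal**
- A path that stays flat at any level has C = 0.
- At one level per session, the highest C for a path ending at level 2 is 1.00 and the lowest for a completer is also 1.00 (1,2,3,3,3,3 | 3,3,3,3,4,5: 21/6 - 15/6). Level 2 can tie but not win.
- Level 2 wins only if the completer gains more than one level in a session or is already above level 1 in session 1. For example, 2,4,5,5,5,5 | 5,5,5,5,5,5 gives 5.00 - 26/6 = +0.67.
- A gradual rise to level 3 (1,1,1,2,2,2 | 3,3,3,3,3,3) gives +1.50, below the fastest completer.

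**How often.** All one-step paths were enumerated with equal weight, which is arbitrary. A path ending at level 3 outscores a completer on C in about 1.8% of pairs, and a path ending at level 4 in about 15%. Mean C still rises with final level: 0, 0.55, 1.09, 1.64 and 2.18 for levels 1 to 5.

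**The case against.** The strongest reply is that the article already contains a score without this defect, the 12-session average, so the point is only one consequence of the disagreement between two sections. That is partly right, and it shapes the remedy. But Target Scores is the section that sets the analysis and its interpretation, and without this point a sponsor could reconcile the sections in the wrong direction.

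The wording in Target Scores is also loose. It does not spell out second-half mean minus first-half mean. That contrast is the natural reading of a change between two named halves, but it is inferred.

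Three stronger readings are tempting, and the documents do not support them:
- A reader might infer that a participant stuck at level 2 or 3 outranks a completer. A participant who stays at one level scores 0. Level 3 must be reached late, and level 2 wins only under the extra conditions shown above. The article does not rule those out, but it describes starting at the lowest level and moving to the next step.
- A reader might infer that the score generally ranks the best engagers low. It does not: on average it still rises with final level, and the reversals are a minority.
- A reader might infer that the association with clinical change will be weakened or reversed. That would require fast climbers to improve more, and nothing in the article establishes this.

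Replacing the change with the highest level alone would not be better, because everyone who finishes would score 5 whether they did so early or late. The average is not perfect either. A late completer (1 for eight sessions, then 2,3,4,5) averages 22/12 = 1.83, below an early plateau at level 3 (1,2, then 3 for ten sessions) at 33/12 = 2.75. But unlike the change, it never falls because a participant climbed sooner.

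**Conclusion.** The point holds in limited form. For the hierarchy level, the magnitude of the half-versus-half change does not reliably reflect engagement. At one level per session, the fastest completer (+1.67) falls below a steady climber who never reaches level 5 (+2.00), a late climber who stops at level 3 (+1.83) and a slower completer (+2.67).

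This rests on reading the score as second-half mean minus first-half mean, on full attendance, and on illustrative paths. The article gives no data on how quickly participants actually climb, so the frequency in the trial is unknown.

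The effect is confined to the exploratory target-engagement analysis and the association under Further Analyses. The feasibility, acceptability, safety and usability outcomes are untouched, as is the decision to proceed, which rests on the user experience survey.

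**What to change.** 1. Under Target Scores, drop the half-versus-half change as the engagement score for the hierarchy level. Use instead each participant's average of the highest level per session, as Psychological Treatment Target already has it, and use the same score under Further Analyses.
2. State the divisor when sessions are missed: one section refers to 12 sessions and the other to sessions attended.
3. Report alongside it, for each participant, the highest level reached and the number of sessions taken to reach it. This covers cases where the average places a late completer below an early plateau.
4. Restrict the sentence that interprets the magnitude of change as engagement to the neural score.

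The cost is wording only. All of these figures come from the per-session level that is already recorded, with no added burden on participants.
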